### Description of the Study

The phases of the study are:

#### Phase 1

Recruitment of the PCT: The project was presented to all of the potential PCTs in order to recruit health professional that were interested in participating. Both doctors and nurses were allowed participate. Those who wanted to collaborate signed a comittment form.

#### Phase 2

Forming the study groups (Intervention group (IG) and non intervention group (NIG)) and training the health professionals.

- The unit of randomization was the center. The centers were assigned to either the IG o the NIG by simple randomization, with a ratio of 1 to 1. The system of randomization was centralized and computerized.

- The professionals in the IG received a specific training program that consists of a motivational interview workshop and a pharmocological treatment workshop specialized for smoking cessation. Both workshops were geared towards diabetic smokers and were taught by experts. The professionals also received training in how to use the electronic data collection system and in the dynamics of the follow-up visits according the Prochaska and DiClemente's Transtheoretical Model of Change. The professionals in the NIG attened practical training session that covered the methodology of the study and how to use the electronic data collection system.

#### Phase 3

Recruitment of the patients and initial categorization in IG and NIG (currently the study is in this phase):

- Selection of patients: Patients were recruited as they visited the PCT. If in the month prior to closing the patient recruitment phase a professional had not recruited the number of patients required, a list of diabetic smokers could be obtained and the necessary number was selected by simple randomization. The professional called the selected patients to make an appointment. According to a previous estimation and taking into consideration the sample size, each professional had to recruit five patients. The form of recruitment, as well as the number of patients to be recruited by each professional, was considered feasible for professionals in routine clinical practice.

- Inclusion of patients: If a patient met the inclusion criteria, the doctor or nurse explained the study to the patient and solicited the patient's participation. If the subject agreed, he or she received information about the study and signed a consent form. If the subject did not wish to participate, the motives were documented.

- Initial categorization of patients: In the first contact with the patient, the following variables were collected using an individualized interview.

- Independent: administrative, sociodemographic, anthropometric, those related with diabetes, associated pathologies and those related to the smoking habit

- Dependent: length of visit

- All of the data is being registered in the electronic data collection system which includes measures to assure consistency and quality control.

- Pilot program: A pilot program will be carried out in subjects that will be excluded from the study so as not to affect the final results. The pilot program aims to evaluate: the process of inclusion of subjects, data collection using the electronic system and the difficulties encountered in the intervention and in the established circuits.

#### Phase 4

Intervention (only in IG): An intensive, individualized intervention using the motivational interview, conduct therapies and medications, adapted according to the stage of change of the patient, will be used. The number of visits will depend on the stage that the patient is in (five for pre-contemplation, seven for contemplation and eight for preparation-action). Patients can move forward and backward in their stage over the course of the study, and the study will adapt to these changes. The phases of the intervention will be detailed in the IG algorithm (see Figure 1).The variables to be collected are specified in the electronic data collection system.

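### Patients are recruited after allocation by professionals who know their arm, so readiness to quit may differ between arms at entry, and the planned adjustment does not fix the covariates that would address it

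*Protocol article*

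**What the plan says.** The order of events is set out under Description of the Study.

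- **Phase 2** is headed "Forming the study groups (Intervention group (IG) and non intervention group (NIG)) and training the health professionals". It states "The unit of randomization was the center" and "The centers were assigned to either the IG o the NIG by simple randomization, with a ratio of 1 to 1". Training then differs by arm: "The professionals in the IG received a specific training program that consists of a motivational interview workshop and a pharmocological treatment workshop". Professionals in the non-intervention group (NIG) are trained only in study methods and the data system.
- **Phase 3** follows. "Patients were recruited as they visited the PCT", and "each professional had to recruit five patients". If a professional is short of the quota in the month before recruitment closes, "a list of diabetic smokers could be obtained and the necessary number was selected by simple randomization". The participating doctor or nurse explains the study and asks for consent. Reasons for refusal are documented. The article says that the study is in this phase at the time of writing.

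The Independent Variables section includes stage of change, the Richmond motivation test and the Fagerström dependence test, and Phase 3 places the smoking-related variables at first contact. The Statistical analysis section plans intention to treat, a baseline comparability analysis, and multilevel logistic and Poisson models on independent variables found significant in bivariate analysis. It adds that all analyses will be adjusted for potential confounders and clinically relevant variables, without naming them. Phase 5 plans a participant flow chart.

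**The concern.** Randomising clusters balances the teams in expectation. It does not balance the patients if they are identified and consented afterwards by people who know the allocation. The different training in Phase 2 reveals the arm, so every invitation in Phase 3 is made with that knowledge. The quota is five per professional, and the sample size section assumes an average of 25 diabetic smokers per team. Under the stated procedure, nothing fixes which of the patients who attend are approached.

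Readiness to quit plausibly predicts abstinence, so a difference in readiness at entry would be read as an intervention effect, or would hide one. Intention to treat preserves the groups as enrolled and so cannot correct who was enrolled. Two features make readiness the natural dimension for such a difference. Patients already in the process of quitting are excluded while preparation-action patients are admitted, and the arm-aware recruiter draws that line. Also, documented refusals cover only patients who were invited, whereas this kind of selection acts on those never approached.

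**Working it through.** **Precision from the plan's own figures.** The article assumes 5% abstinence in NIG, a 12-point difference, two-sided alpha 0.05, power 0.80, 20% loss, intracluster correlation 0.05 and 25 patients per team.

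- The arcsine formula for 5% against 17% gives 98.6 per group. Dividing by 0.80 gives 123.3, rounded up to the stated 124.
- Design effect: 1 + (25 − 1) × 0.05 = 2.2.
- 2 × 124 × 2.2 = 545.6, rounded up to 546. 546 / 25 = 21.8, rounded up to 22 teams.

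The plan's figures reproduce, so they can be used for precision. Effective number per arm: (546 / 2) × 0.8 / 2.2 = 99.3.

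**Illustration, with assumptions that are not in the document.** There is no intervention effect. Abstinence is 14% in preparation-action entrants and 2% in all others. NIG abstinence is the article's 5%, which implies a preparation-action share of (0.05 − 0.02) / (0.14 − 0.02) = 25% in NIG. The comparison is unadjusted.

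Spurious difference = difference in share × (0.14 − 0.02).

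SE = √[p₀(1 − p₀)/99.3 + p₁(1 − p₁)/99.3], with p₀ = 0.05 and p₁ = 0.05 + spurious difference.

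Two-sided rejection probability = P(Z > 1.96 − d/SE) + P(Z < −1.96 − d/SE), where d is the spurious difference.

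| Share, NIG vs IG | d | p₁ | SE | d/SE | Type I error |
|---|---|---|---|---|---|
| 25% vs 35% | 0.10 × 0.12 = 1.2 points | 6.2% | 3.26 points | 0.37 | 0.056 + 0.010 = 6.6% |
| 25% vs 40% | 0.15 × 0.12 = 1.8 points | 6.8% | 3.34 points | 0.54 | 0.078 + 0.006 = 8.4% |

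The table puts the higher share in the intervention group (IG). With the shares reversed, the spurious difference has the same size and favours NIG.

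**Sensitivity to the assumed rates.** With shares of 30% and 40%, abstinence of 10% vs 3%, 15% vs 3% and 20% vs 4% by readiness gives spurious differences of 0.10 × 0.07 = 0.7, 0.10 × 0.12 = 1.2 and 0.10 × 0.16 = 1.6 points.

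**What the planned model guarantees.** The Statistical analysis section has two routes into the model. Bivariate significance may drop a predictor that is imbalanced between arms but narrowly misses the threshold. The general adjustment clause is not tied to significance but names no variable. Neither route guarantees that stage, Richmond or Fagerström scores enter the primary model. Recruitment route is not among the listed variables, and nothing is stated about counting eligible patients who were not approached.

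**The case against.** The strongest reply has four parts.

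**Choice is not in the text.** Recruiting patients as they attend is compatible with consecutive enrolment, and a condensed article may leave the operational rule to the full protocol. This stands. The article shows an opportunity for selection, not that selection occurs.

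**The direction is unknown.** A reader might infer that IG professionals, facing a heavy visit schedule, would favour motivated smokers. Phase 4 does not support that: it plans five visits for pre-contemplation, seven for contemplation and eight for preparation-action, so the readiest patients bring the most work. Nor is there evidence that NIG professionals are indifferent, since both arms volunteered and both follow patients to one year. This stands too.

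**The bias may be small.** A reader might push the illustration to a 35-point gap in share, giving 0.35 × 0.12 = 4.2 points and, with the SE held at its 5%-in-both-arms value of 3.1 points, a type I error of 27%. With the arm rates that this scenario implies (5% and 9.2%), the SE is 3.6 points and the error about 21%. It would also require 60% of IG patients in preparation-action, although the Background says most diabetic smokers are pre-contemplative. That figure should not be relied on. All these error rates also ignore the planned adjustment.

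**Safeguards exist.** Readiness is measured, comparability examined, refusals documented, a flow chart planned and adjustment promised, and naming covariates is often left to an analysis plan. This stands in part. The article nevertheless does state a selection rule for covariates, by bivariate significance, and that rule suits this purpose badly. Adjustment also covers only measured factors. Baseline stage is itself recorded by arm-aware staff, and training in visits organised around the stage model is described only for IG.

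**Conclusion.** The point holds as a risk of recruitment bias after randomisation, of unknown direction and size, that the planned safeguards only partly cover. The order of randomisation, arm-specific training and recruitment is explicit. Knowledge of the arm follows from the different training, although the article does not say so in words.

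Under the assumed abstinence rates, and with a 10 to 15 point difference in preparation-action share, the spurious difference is 1.2 to 1.8 points against a planned effect of 12, and the unadjusted type I error is about 7% to 8%. This is modest but aimed at the primary endpoint. The document supplies neither the abstinence rates by stage nor the imbalance, so these figures show a scale and are not estimates.

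The article does not support the stronger readings that professionals select motivated patients, that the bias favours the intervention, or that the trial is invalid.

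**What to change.** 1. In the Statistical analysis section, replace selection by bivariate significance, for the primary abstinence model, with a fixed set of baseline covariates: stage of change, Richmond score and Fagerström score. Enter them in the multilevel logistic regression regardless of significance. All three are already collected, so this costs nothing.
2. For remaining recruitment in both arms, record each patient's recruitment route (at a visit or from the list) and the numbers eligible, approached and refusing by arm. Report these in the flow chart already planned. The cost is minor extra recording by the professionals.
3. State in the protocol and the report that adjustment cannot remove selection on unmeasured factors.

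Making the random list the main route for the remaining patients is a debatable trade and is not proposed here. Patients already enrolled would remain opportunistic, the mix of routes could then differ by arm, and the same arm-aware professional would still make the call and seek consent. The article also says that the present form of recruitment was considered feasible in routine practice.

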**Figure 1 F1:**
[figure not shown]
**ITADI Intervention group study algorithm**.

The patients of the NIG group will receive the usual care in PC, and at the end of the study, the NIG professionals will also be trained in the motivational interview and in pharmocological treatments.

#### Phase 5

Final categorization (in IG and NIG): The dependent variables will be collected in all subjects at one-year post- inclusion. The motives for withdrawl and loss of follow-up from the study will be recorded and a flow chart of participants will be created over the course of the study.

#### Phase 6

End of data collection: Data collection will be concluded after carrying out the final patient categorization. Because of the periodic monitoring of the data in the electonic data collection system, incoherencies will have been located and corrected.

#### Phase 7

Data analysis and diffusion of results: The collected data will be analyzed, the final report will be elaborated and the results will be diffused in various scientific outlets.

### Statistical analysis

Data will be analyzed in concordance with the Consort Cluster guide [31], and all analyses will be done on an intention to treat basis. A descriptive analysis and an analysis of baseline comparability between the study groups will be performed for the variables studied. A T-student test or a U Mann Whitey will be used to compare means with two categories, an ANOVA test will be done to compare means with two or more categories, and a Chi- squared test or a Chi -squared tendency test will be done to compare categorical variables. A multilevel logistic regression and a Poisson regression will be done to evaluate the association between each of the dependent variables and the independent variables that have resulted statistically significant in the bivariate analisis. All analisis will be adjusted for potential confounding factors and for variables with clinical relevance. All tests will be done with a 95% bilateral confidence interval. SPSS 15, STATA 10 and HLM6 will be used.

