## Methods/Design

### Design

Cluster randomized trial, controlled and multicentric. Randomization unit: Primary Care Team (PCT).

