### Sample size calculation

The sample size has been calcuated by multipying the size of a randomized simple design by the design effect. In the simple randomized design, considering an alpha error of 0.05 a beta error of 0.20 in a bilateral contrast, and given that 15% of diabetics are smokers, 124 subjects were needed in each study group in order to determine a difference in continued abstinence of greater than or equal to 12% between study groups. A continued abstinence of 5% was assumed for the non intervention group, and a potential loss of follow-up of 20% was estimated.

Using an intracluster correlation coefficient of 0.05 [28-30], and based on an average of 25 diabetic smokers per PCT, the design effect is 2.2. Therefore, 546 diabetic smokers and 22 PCT were needed. The sample size was calculated using the Granmo 5.2 program for Windows.

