#### Independent Variables

• Variables related to the patient (information obtained through an individualized interview):

- Administrative: PCT, PC professional, data collection date, patient code.

- Sociodemographics: date of birth, sex, level of education.

- Anthropometric: weight, height.

• Related to diabetes: type, year of diagnosis, type of treatment, presence of complications related to diabetes (peripheral arterial disease, ischemic heart disease, retinopathy, neuropathy, nephopathy).

• Related to associated pathologies: COPD, cerebrovascular accident, isquemic heart disease, hypertension, hypercholesterolemia.

• Variables related to tobacco consumption: age at initiation of habit, number of cigarettes per day, nicotine dependence (Fagerström test), motivation to quit (Richmond test), number of previous attempts to quit for at least 24 hours, smoking cessation treatment with mediciations, maximum time of abstinence, phase of the patient according to Prochaska and DiClemente's model (pre-contemplation, contemplation, preparation-action), tobacco in usual environment (family, partner, friends, coworkers, classmates), perceived grade of harmfulness of tobacco on diabetes, point prevalence abstinence (smoking abstinence at the time of the visit and with a CO level of less than 6 ppm), length of abstinence.

• Variables related to the intervention: attendance of intervention visit, date of intervention visit, date of D day, time spent on intervention visit, medication used for smoking cessation, relapse, reason for relapse, CO level in breath, observations.

• Variables related to the one-year follow-up visit: attendance to follow-up visit, date of follow-up visit, smoking status, number of cigarettes per day, length of abstinence, phase of the patient according to Prochaska and DiClemente's model (pre-contemplation, contemplation, preparation-action), CO level in breath, observations.

• Variables related to the PCT: years the PCT has been operating, assigned population, mean age of assigned population, whether or not it is a teaching center for residents, number of doctors, number of nurses, number of social workers, other specializations, number of centers.

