## Discussion

Although there are studies that use intensive interventions in smoking cessation such as the ISTAPS study [20], the majority are directed towards the general population. The challenge of the present study is to exclusively direct the intervention towards diabetic smokers in PC. The fact that these type of patients are resistant to change should not be an obstacle, as it is a priority to address the topic of smoking when dealing with patients with an elevated cardiovascular risk. Furthermore, it should be kept in mind that the intention of this intervention is not only to achieve continued smoking abstinence, but also to achieve partial goals, such as advancing in the stages of change of Prochaska and DiClemente and the reduction of the number of cigarettes smoked per day. These partial goals can motivate a healthcare professional who has tried unsuccessfully on several occasions to get his or her patient to quit smoking, to continue working towards progress.

One of the stengths of the ITADI study is the population of the study, diabetic patients that attend PC. Another strength is the design of the study, which is pragmatic in terms of time and material resources needed. If the hypothesis of the present study is confimed, it could be incorporated into current PC clinical practice guidelines. The large number of healthcare professionals and patients involved in the present study is another strength, as it reinforces the external validity of the data.

The randomization has been done by PCT and not by patient, so as to avoid the unethical situation in which a healthcare professional would feel obligated to use the motivational interview and pharmocotherapy in only some of his or her patients. This will also prevent contamination between healthcare professionals of the same center. Although the unit of randomization is the center, the intervention is given at the individual level and the outcomes are also measured at this level. The estimation of the design effect will be taken into account in all of the main analyses.

The motivational interview techiques require personal communication and empathy from the part of the healthcare professional towards his or her patient. The training sessions are one full day, although it is known that the more training the professional has in motivational interviewing, the more he or she is able to apply the learned skills [32].

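### The group and bivariate tests ignore clustering by PCT: at the protocol's ICC, a nominal 5% test of an arm difference or a PCT-level variable has a true size of about 12% to 19%

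*Protocol article*

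**What the plan says.** The Design section makes the PCT the unit of randomisation, and the Description of the Study says that centres were allocated "by simple randomization, with a ratio of 1 to 1". The Sample size calculation allows for clustering: with an ICC of 0.05 and "based on an average of 25 diabetic smokers per PCT, the design effect is 2.2".

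The Statistical analysis section announces a baseline comparison of the study groups and then lists the tests: "A T-student test or a U Mann Whitey will be used to compare means with two categories", ANOVA for means across categories, and chi-squared or chi-squared trend tests for categorical variables. It mentions no allowance for clustering in any of them. It then plans a multilevel logistic regression and a Poisson regression relating each dependent variable to the "independent variables that have resulted statistically significant in the bivariate analisis". It adds adjustment for potential confounders and clinically relevant variables, and says that the analysis will follow the CONSORT guidance for cluster trials.

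The Discussion says: "The estimation of the design effect will be taken into account in all of the main analyses". It does not mention the bivariate step. The candidate variables include a PCT-level block that begins "Variables related to the PCT: years the PCT has been operating, assigned population, mean age of assigned population" and goes on to teaching status, numbers of doctors, nurses and social workers, other specialisations and number of centres. That makes nine variables.

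**The concern.** The named tests treat every patient as an independent observation. In a trial that allocates PCTs, their null hypothesis is therefore that the groups do not differ and that PCTs do not vary. The protocol assumes that PCTs do vary. A test that ignores this uses a standard error that is too small, and it can reject merely because PCTs differ from one another.

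Two uses are exposed. One is any comparison of the arms made with these tests, such as baseline comparability. The other is the screening of PCT characteristics against an outcome: they are constant within a PCT and so take the full design effect. At stake are the p-values reported for these comparisons, and PCT characteristics carried into the models and reported as associated with an outcome when they are not.

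**Working it through.** **Inputs.** From the Sample size calculation: two-sided alpha 0.05, power 0.80, 5% abstinence in the control group, a difference of 12 points, 20% loss, ICC 0.05, 25 patients per PCT, design effect 2.2, 546 patients and 22 PCTs. From the Setting: 43 PCTs. The ICCs of patient-level covariates are not given, so they are assumptions shown as a range.

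**1. The plan's own figures.** The arcsine formula for 5% against 17% gives 98.6, so 99 per group. Then 99/0.80 = 123.75, so 124. Design effect = 1 + (25 − 1) × 0.05 = 2.2. Total = 2 × 124 × 2.2 = 545.6, so 546. PCTs = 546/25 = 21.8, so 22. The stated sample size reproduces.

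**2. True size of a patient-level 5% test between arms, or on a PCT-level variable.** With design effect DE, size = 2 × P(Z > 1.96/√DE).

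| Scenario, ICC 0.05 | Patients per PCT | DE | True size |
|---|---|---|---|
| 22 PCTs | 25 | 2.20 | 18.6% |
| 22 PCTs, 20% loss | 20 | 1.95 | 16.0% |
| 43 PCTs share 546 patients | 12.7 | 1.58 | 12.0% |
| 43 PCTs, 20% loss | 10.2 | 1.46 | 10.5% |

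Simulation under no difference agrees. With 22 PCTs of 25, the chi-squared test rejected 18.5% to 19.8% of the time (beta-binomial data, prevalence 5% to 50%) and the t-test 18.4%. With 42 PCTs of 13, the figures were 12.0% to 12.8% and 12.0%. A t-test on PCT means held 4.6% to 5.1%.

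**3. Sensitivity to the ICC.**

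| ICC | 25 per PCT | 12.7 per PCT |
|---|---|---|
| 0.01 | 7.8% | 6.4% |
| 0.02 | 10.7% | 7.8% |
| 0.10 | 28.8% | 18.3% |

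**4. The nine PCT-level candidates.** If none is associated with the outcome, the expected number selected is 9 × 0.186 = 1.7 (22 PCTs) or 9 × 0.120 = 1.1 (43 PCTs). At the nominal level it is 9 × 0.05 = 0.45.

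**5. Patient-level candidates.** For a covariate with its own ICC, DE is approximately 1 + (25 − 1) × 0.05 × ICC of the covariate.

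| Covariate ICC (assumed) | DE | True size | Simulated |
|---|---|---|---|
| 0 | 1.00 | 5.0% | 5.3% |
| 0.05 | 1.06 | 5.7% | 5.5% |
| 0.10 | 1.12 | 6.4% | 6.2% |

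**6. Does false selection harm the intervention test?** This was simulated with no intervention effect, ICC 0.05 and nine irrelevant PCT-level candidates, which were screened and then adjusted for in a linear model on PCT means (8,000 runs). With 22 PCTs the patient-level screen selected 1.68 variables and a cluster-level screen 0.46. The intervention test then rejected 5.0% and 4.8% of the time, against 4.9% with no covariates. The standard deviations of the estimate were 0.122, 0.122 and 0.127. With 43 PCTs the rejection rates were 5.2%, 5.2% and 5.0%. This is a linear stand-in, not the logistic model itself.

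**The case against.** The strongest reply is that the analyses that matter already allow for clustering. The logistic regression is multilevel, the Discussion commits to the design effect in the main analyses, and the CONSORT cluster guidance is cited. This stands for the primary comparison. A reader might infer that the primary test runs at 19%, or that false selections distort the intervention estimate. The documents do not support the first, because the primary model is multilevel. The simulation in step 6 gives no support to the second.

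A reader might also infer that the whole screen runs at 19%. It does not. Most candidates are patient-level (sociodemographic, diabetes, comorbidity and smoking variables) and are screened at about 5% to 6% if their clustering is modest. Nor is the screen the only route into the models, since confounders and clinically relevant variables enter as well.

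It is also tempting to say that total time can be tested only by the t or Mann-Whitney test. The text does not say so: time is a listed dependent variable, and the regressions are assigned to each dependent variable.

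Two further limits are fair. The 19% rests on 22 PCTs of 25, while the Setting names 43. And 0.05 is the ICC used to size the abstinence comparison; no ICC is given for baseline variables.

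What remains is that the article itself states the tests and the entry rule, so this is not detail left to an analysis plan. A general citation of guidance does not change the tests named after it, and the Discussion's commitment does not mention the bivariate step.

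**Conclusion.** The point holds in a limited form. The tests named for group and bivariate comparisons ignore the clustering that the protocol assumes. At ICC 0.05 their true size is about 19% (22 PCTs of 25), 16% (after 20% loss) or 12% (43 PCTs sharing 546 patients), not 5%. This covers arm comparisons of variables that have that ICC, and the nine PCT-level variables screened against an outcome with that ICC. About 1.1 to 1.7 of the nine would be selected and reported as associated by chance, against 0.45 nominally.

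For other variables the inflation depends on an ICC that the documents do not give. The primary result is not shown to be at risk. The change is still worth making, because a stated rule yields p-values that are too small and the repair is cheap.

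**What to change.** In the Statistical analysis section, specify cluster-respecting versions of these tests for arm comparisons and for the bivariate screen, at least for the PCT-level variables. Suitable choices are a model with a PCT random intercept, a design-effect-adjusted test, or a t-test on PCT means with degrees of freedom based on the number of PCTs. Extend the Discussion's commitment on the design effect from the main analyses to the bivariate analyses.

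The cost is wording and a little more programming. The listed software includes HLM6 and STATA 10, and no new patients or data are needed. The article describes recruitment as still under way, so the change can be made before analysis. The downside is larger p-values and wider intervals for these comparisons.

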### Data Collection

#### Dependent Variables

• Continued abstinence (yes, no) is defined as at least six months without smoking and a CO breath level of <6 ppm, measured by a cooximeter in standard conditions.

• Stage change in Prochaska and DiClemente's Transtheoretical Model of Change (advance, maintained, backwards, relapse).

• Number of cigarettes per day, reported by the patient.

• Total time (in minutes) spent on the intervention.

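### The covariate rule screens variables on bivariate significance and does not exclude those measured after randomisation, including the components of the primary outcome

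*Protocol article*

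**What the plan says.** The Statistical analysis section gives one model-building rule. Multilevel logistic and Poisson regressions are to evaluate the "association between each of the dependent variables and the independent variables that have resulted statistically significant in the bivariate analisis". A further sentence adds: "All analisis will be adjusted for potential confounding factors and for variables with clinical relevance". Neither sentence says when a covariate must have been measured.

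The Independent Variables section supplies the list. Besides patient and team characteristics, it has two bullets of later data:

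- **Intervention:** visit attendance and dates, then "time spent on intervention visit, medication used for smoking cessation, relapse, reason for relapse, CO level in breath".
- **One-year visit:** "attendance to follow-up visit, date of follow-up visit, smoking status, number of cigarettes per day, length of abstinence", followed by stage of change and CO level.

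The Dependent Variables section defines the primary outcome: "Continued abstinence (yes, no) is defined as at least six months without smoking and a CO breath level of <6 ppm".

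The Description of the Study restricts Phase 4 to one arm: "Intervention (only in IG): An intensive, individualized intervention using the motivational interview, conduct therapies and medications". For first contact, it labels the administrative, sociodemographic, anthropometric, disease and smoking-habit items as independent. For Phase 5 it says that the dependent variables are what is collected at one year.

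**The concern.** An effectiveness estimate from a randomised trial should be adjusted only for variables that the allocation cannot have changed. Here a named list and a selection rule, read together, admit variables that the intervention is designed to change (medication, visit time, relapse) and variables from which the outcome is built (length of abstinence, CO). These last are strongly associated with the outcome by construction, so they are the likeliest to pass a bivariate screen.

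The principal objective is at stake. If such variables enter, the group coefficient no longer describes the effect of being allocated to the intervention, even though every patient is analysed in the allocated arm. If the analyst decides case by case which of them to leave out, the adjusted effect depends on choices made after the results are seen.

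**Working it through.** **1. The plan's own figures.** The inputs are in the sample size section: 5% against 17% abstinence, two-sided alpha 0.05, power 0.80, loss 20%, intracluster correlation 0.05, 25 patients per team.

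- Arcsine formula: h = 2·asin(√0.17) − 2·asin(√0.05) = 0.399; n = 2 × (1.960 + 0.842)² / 0.399² = 98.6, so 99 per group; 99 / 0.8 = 124.
- Design effect: 1 + 24 × 0.05 = 2.2; 2 × 124 × 2.2 = 545.6, so 546; 546 / 25 = 21.8, so 22 teams.

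The stated size reproduces. The target effect as an odds ratio is (0.17/0.83) / (0.05/0.95) = 3.89.

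**2. Which list does the rule draw on?**

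| Item | Independent Variables section | Elsewhere in the article |
|---|---|---|
| One-year length of abstinence, CO | listed | components of the primary outcome |
| One-year cigarettes per day | listed | a dependent variable |
| One-year stage | listed | source of the stage-change outcome |
| Intervention-visit medication, relapse | listed | Phase 4, intervention group only |

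Phase 5 treats one-year data as dependent. The Statistical analysis section uses the term independent variables without choosing between the two usages.

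**3. Outcome components in the model.** Let L = 1 for at least six months without smoking and C = 1 for CO below 6 ppm. By definition the outcome is Y = L × C. The expression L + C − 1.5 is positive exactly when Y = 1, so a logistic model containing both indicators is completely separated. It has no finite maximum-likelihood estimate and the group effect cannot be estimated. This step needs no assumed rates. If both enter as continuous measurements, separation need not be exact, but almost nothing is left for group to explain.

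**4. Mediators in the model.** The article gives no rates of medication use or of quitting by use, so only a range can be shown. Every rate below is assumed; each row is set to give about 17% and 5% overall. IG is the intervention group and NIG the non-intervention group.

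| Medication use IG / NIG | Quit rate with / without, IG | Quit rate with / without, NIG | Group OR unadjusted | Group OR adjusted for medication |
|---|---|---|---|---|
| 35% / 5% | 17% / 17% | 5% / 5% | 3.9 | 3.9 |
| 35% / 5% | 25% / 12.7% | 12% / 4.6% | 3.9 | 2.9 |
| 35% / 5% | 33% / 8.5% | 24% / 4% | 3.9 | 2.0 |
| 45% / 5% | 33.5% / 3.5% | 33.5% / 3.5% | 3.9 | 1.0 |

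Check on the third row: 0.35 × 0.33 + 0.65 × 0.085 = 0.171 and 0.05 × 0.24 + 0.95 × 0.04 = 0.050. The odds ratio runs from no attenuation, when medication does not predict quitting, to none of the effect left, when all of it acts through medication.

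**5. One-arm variables.** Intervention-visit data arise in Phase 4, which NIG patients do not undergo. If the fields are missing in NIG, a complete-case model drops that arm and has no group contrast. If they are coded zero, they are largely collinear with group, and the group term compares NIG with IG patients who did not attend or took no medication. The medication table therefore also assumes NIG records that the article does not clearly provide for. Time is a partial exception, since the first-contact visit length is recorded and the third secondary objective compares time with usual practice.

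**6. Screening among baseline items.** Expected abstainers: 546 × 0.8 / 2 = 218.4 per arm; 218.4 × (0.05 + 0.17) = 48. With no losses it would be 273 × 0.22 = 60. Leaving out administrative fields and counting grouped items once, the list has 3 sociodemographic, 2 anthropometric, 4 diabetes, 5 associated-pathology, 12 tobacco and 9 team items, 35 in all. That is 48 / 35 = 1.4 abstainers per candidate, so which covariates pass depends heavily on chance.

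**The case against.** The best defence is that the Independent Variables section sits under Data Collection and is an inventory of form fields; it includes dates and free-text observations that nobody would model. The phase descriptions separate first-contact independent variables from one-year dependent ones. On that reading the one-year fields are raw material for the outcome, and a competent analyst would not enter them. This shows that the article is ambiguous, not that it intends to regress the outcome on itself. But the analysis rule does not refer to the first-contact subset, and the defence does not reach the intervention-visit variables. Intention to treat fixes who is analysed in which arm, not which covariates enter. The sentence on confounders adds to the screen without limiting it.

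Three stronger readings are tempting and are not supported:

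- A reader might infer that the intervention effect would be adjusted away. The article does not show this. The loss depends on rates it does not give, and a separated model would usually fail visibly instead of returning a quiet null.
- A reader might infer that study group could be screened out because it is not listed. The hypothesis, principal objective and sample size are all between-group contrasts; an article may leave retention of the group term unsaid.
- A reader might count point-prevalence abstinence as post-randomisation. It is listed with the tobacco-consumption items and its timing is not stated.

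It is also fair that a bivariate screen could serve the stated aim of profiling patients who benefit. No separate effect model is described, however, so the same rule governs both purposes.

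**Conclusion.** The concern holds as a defect in a stated rule: it selects on bivariate significance from a list that includes post-randomisation variables and does not exclude them. The separation result follows from the outcome definition alone, provided both components enter as the defining indicators. The attenuation is a range, an odds ratio between 3.9 and 1.0, and rests wholly on assumed rates. The one-arm problem follows from Phase 4, provided intervention-visit data are not recorded in NIG by some other route. The instability of screening rests on about 48 abstainers under the plan's own rates, equal arms and 20% loss. The sample size is not affected. Because the article fixes the rule and the list, this is not detail left to an analysis plan.

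**What to change.** Replace the rule for the effectiveness analyses:

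- Estimate the effect on continued abstinence with a multilevel logistic model that always contains study group and a random intercept for primary care team.
- Adjust only for a short list of baseline covariates, named before outcome data are examined.
- State that no variable measured after inclusion enters any effectiveness model. Use intervention-visit data descriptively and one-year data only to construct outcomes.
- Drop bivariate significance as the entry criterion for these models. If it is kept at all, confine it to a separate model, labelled exploratory, of the profile of patients who benefit.
- Reconcile the Independent Variables section with Phase 5, so that one-year items are not listed as independent variables.

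The cost is wording. No new data, visits or patients are needed. The article describes the trial as still recruiting, so at that stage the change could be made before outcome analysis.
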